## Methods and analysis

### Study design

The study consists of a single-arm feasibility trial with a nested qualitative study, and is conducted in collaboration with the Early Intervention (EI) teams from the Avon and Wiltshire Mental Health Partnership NHS Trust (AWP). All participants will be offered EMDR, and will be assessed at baseline, 4, 8 and 12 months of follow-up as described below.

The study design outlined is the final version of the trial protocol. The original protocol was changed as a result of low recruitment. Recruitment challenges are described later.

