### Challenges to recruitment

The original feasibility study was designed as an RCT comparing EMDR with TAU. TAU in AWP is quite heterogeneous and consists of discharge back to the referrer, signposting to other services, CBT, family intervention or psychoeducation. Randomisation took place using a remote computerised randomisation service administered by the Bristol Trials Centre ensuring that allocations were concealed from the recruiting researcher. Randomisation was minimised by psychotic symptom severity (score on positive symptoms on CAARMS <11 or ≥11). However, following challenges to recruitment (described below), the study design was changed to a single-arm study.

During the first 7 months of the study (May to December 2018), we only recruited three participants (against a target of 21). This poor recruitment was primarily because the number of patients identified as ARMS by the EI teams within AWP was much lower than expected, and only three of the six EI teams we originally planned to recruit from were able to support the study due to financial constraints to managing ARMS clients. Therefore, from July 2019, all participants recruited to the study were offered EMDR. Figure 1 shows the flow of participants in the randomised and single-arm phases of the trial.

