### Sample size and feasibility of recruitment

In the original protocol we had planned to recruit up to 40 participants. The initial sample size was informed by literature guidelines^34^ and pragmatic considerations concerning potential difficulties accessing this population. The feasibility study would not be powered to detect important clinical differences between EMDR and TAU groups but would provide estimates of the completion and retention rates that would further assist in planning the recruitment for a future RCT.

Given the challenges with recruitment and modification of our study design (from a randomised to single-arm trial), we decreased our target sample size from 40 to 20 participants. This sample size will provide us with reasonable precision around estimates of percentages completing the intervention and follow-ups. For example, if 70% of those who started EMDR complete the intervention, the 95% CIs would be 45% and 88%. Similarly, if 75% of those who started EMDR are followed up to 12 months, the 95% CIs for the retention rate would be 50% and 91%.

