### Primary outcome

Transition to psychosis: ICD-10 diagnosis of psychotic disorder from clinical records or via the CAARMS.

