### Quantitative data analysis

Quantitative data will be analysed in Stata V.15.^35^ If there are no differences in baseline characteristics of those who were randomised and those who enter the single-arm study, we will combine data to generate summary statistics on: (1) the proportion consenting to take part in the study; (2) the proportion completing the baseline assessment and agreeing to take part in the study; (3) the number of EMDR sessions attended and the proportion completing eight or more sessions (regarded as an adequate dose of therapy); (4) the proportion completing the follow-up assessments. Feasibility outcomes such as recruitment and retention rates will be calculated with 95% CIs using the exact binomial method.

We will also report the proportion of individuals who transitioned to psychosis at 12 months, and the CIs for the effect size will be calculated to assist the planning of a future RCT. We will also compare the continuous outcomes such as the severity of psychotic symptoms, depression, anxiety, PTSD symptoms and quality of life to show the frequency of data completion, mean and SD for the three time points.

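### The analysis plans confidence intervals for an effect size on transition to psychosis, but the single-arm design names no comparator from which a treatment effect could be estimated

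*Protocol article*

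**What the plan says.** All references are to the protocol article.

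- **Study design:** "The study consists of a single-arm feasibility trial with a nested qualitative study". It continues: "All participants will be offered EMDR, and will be assessed at baseline, 4, 8 and 12 months of follow-up".
- **Challenges to recruitment:** "The original feasibility study was designed as an RCT comparing EMDR with TAU". After the change, "from July 2019, all participants recruited to the study were offered EMDR".
- **Primary outcome:** "Transition to psychosis: ICD-10 diagnosis of psychotic disorder from clinical records or via the CAARMS".
- **Quantitative data analysis:** the 12-month transition proportion will be reported, and then "the CIs for the effect size will be calculated to assist the planning of a future RCT". The effect size is not defined, and no control group, historical rate or reference value is given. Continuous outcomes are to be summarised by "mean and SD for the three time points".
- **Sample size and feasibility of recruitment:** the feasibility study as first planned, with up to 40 participants, "would not be powered to detect important clinical differences between EMDR and TAU groups". The reduced target of 20 is justified only by the precision of the completion and follow-up percentages.
- **Feasibility trial status:** six participants had been recruited before the July 2019 switch, and 14 in total by July 2020, after recruitment had closed.

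**The concern.** A treatment effect on a binary outcome is a contrast between two risks, and a single arm supplies one. The clause would make sense in an EMDR v TAU trial. In the current design it has no defined quantity behind it, and it concerns the named primary outcome.

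An analyst following the text would have to choose a comparator after the fact: the few participants randomised to TAU, all EMDR participants against those few, or the 22% one-year risk cited in the Introduction. The choices answer different questions, and none gives a usable treatment effect. Because the result is meant to help plan the RCT, a chance finding of very few transitions could be read as evidence of benefit.

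**Working it through.** **1. The plan's own precision figures.** The article gives intervals for completion and retention at n = 20 and specifies the exact binomial method. The Clopper-Pearson limits for x events in n are the 2.5% quantile of Beta(x, n-x+1) and the 97.5% quantile of Beta(x+1, n-x).

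| Quantity | x/n | Stated | Recomputed |
|---|---|---|---|
| Completion 70% | 14/20 | 45% to 88% | 45.7% to 88.1% |
| Retention 75% | 15/20 | 50% to 91% | 50.9% to 91.3% |

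The stated limits agree when truncated to whole percents. They are one-sample proportions. The article gives no precision figure for an effect size.

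**2. What contrasts the data could hold.** The inputs are six participants recruited before the switch and 14 in all, so 14 - 6 = 8 were recruited afterwards, all offered EMDR. The TAU number among the six is not in the text (Figure 1 is not shown). Splits and event counts below are therefore assumptions.

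*Randomised participants only.* The Newcombe interval for p1 - p2 uses the Wilson limits (l, u) of each proportion:

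- lower = (p1 - p2) - √[(p1 - l1)² + (u2 - p2)²]
- upper = (p1 - p2) + √[(u1 - p1)² + (p2 - l2)²]

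Take 0/3 on EMDR v 1/3 on TAU. The Wilson limits are 0 to 0.5615 and 0.0615 to 0.7923.

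- lower = -0.3333 - √[0² + 0.4590²] = -0.792
- upper = -0.3333 + √[0.5615² + 0.2718²] = +0.291

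Other assumed results:

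| EMDR v TAU | Risk-difference 95% CI (points) |
|---|---|
| 0/3 v 1/3 | -79 to +29 |
| 1/3 v 1/3 | -53 to +53 |
| 0/3 v 0/3 | -56 to +56 |
| 0/4 v 1/2 | -90 to +14 |
| 0/2 v 1/4 | -70 to +44 |

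Every interval includes zero and spans more than 100 percentage points.

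*All EMDR against the TAU participants.* Assuming 3 TAU, the EMDR group is 14 - 3 = 11. For 2/11 v 1/3 the interval is -63 to +25 points. Eight of those 11 had no chance of being allocated to TAU, so treatment is mixed with recruitment phase. The article's rule for combining phases covers four feasibility summaries and does not set up this comparison.

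*Against the cited 22%.* No such comparison is stated. It would be uncontrolled, and the Secondary outcome section accepts that researchers can no longer be blinded.

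**3. What the single arm can give.** This is the transition proportion with an exact 95% CI. With 2 transitions (assumed), over the possible sizes of the EMDR group:

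| EMDR participants | 2/N | Exact 95% CI |
|---|---|---|
| 8 | 25% | 3% to 65% |
| 11 | 18% | 2% to 52% |
| 14 | 14% | 2% to 43% |

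Each interval contains 22%. Even the valid quantity says little about whether EMDR changes the risk.

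**The case against.** The strongest reply is that effect size is loose wording for the transition proportion, whose interval is then promised. On that reading the plan already does the right thing and only a term is wrong. The reading is possible, but the clause follows the proportion as an addition to it, and nothing in the article equates the two. An analysis plan that is not shown might define the term, but it could not create a concurrent control.

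A reader might infer that the trial's estimate will set the RCT's target difference and so lead to an underpowered trial. The documents do not support that. The stated purpose is only to assist planning, none of the listed objectives is efficacy estimation, and the article links the RCT's power to the retention rate. The wide intervals would themselves warn a careful user.

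A reader might also infer that no comparator exists anywhere in the data, or that the clause is a leftover from the two-arm protocol. The first goes too far, because some of the six early participants may have been allocated to TAU. The second is plausible but cannot be confirmed, since the superseded analysis text is not shown.

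Finally, the three time points for continuous outcomes match the follow-ups at 4, 8 and 12 months and appear to leave out baseline. It does not follow that change from baseline will go unreported; a condensed article may leave that detail to the full plan.

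**Conclusion.** The point holds for the effect-size clause. As written, the plan promises an interval for a quantity that the single-arm design cannot supply and for which it names no comparator. The only randomised contrast rests on at most six people. Under the splits and event counts tried, its interval spans more than 100 points, and the wider non-randomised contrast is confounded by phase. These sizes rest on assumed splits and counts; the lack of a comparator in the current design does not.

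This should be fixed, but it is not critical. It affects one clause of a feasibility analysis and leaves the recruitment, completion and retention estimates untouched.

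**What to change.** In Quantitative data analysis, replace the effect-size clause with text to this effect:

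- Transition by 12 months among participants offered EMDR will be reported as n/N with an exact 95% CI and described as uncontrolled.
- Any participants randomised to TAU will be listed descriptively.
- Neither result will be used as the effect estimate for the RCT. Its assumed effect will come from an external control risk and a minimum important difference.

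Optionally, show baseline values beside the 4-, 8- and 12-month means and SDs.

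The cost is wording only. The exact method is already specified for the feasibility outcomes, baseline measures are already collected, and no new data are needed. Follow-up was expected to run to May 2021, so on the article's own timetable the change could precede the analysis.

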### Qualitative data collection

We will conduct in-depth individual interviews with all the therapists and participants who participate in the trial. In addition, up to 10 individuals who declined to take part in the trial will be interviewed to explore their views and understanding of the study and EMDR, and their reasons for declining to take part.

To encourage participation, and because well-planned interviews can gather the same material as those conducted face to face,^36^ therapists and study participants will be given the choice of being interviewed in person or over the telephone. Therapists will be interviewed within a month of finishing intervention delivery. The interviews will explore therapist views and experiences of delivering EMDR to patients with ARMS, how treatment could be better tailored to this patient group and what resources they would need if the intervention was evaluated in a large-scale RCT. The interviews will also be used to explore their views of the training and supervision received.

Interviews with participants who completed treatment or stopped early will explore their views and experiences of the treatment received, identify how treatment delivery could be refined to increase its acceptability and how study materials could be improved. Participants who completed the study will be interviewed within a month of completing their 4-month follow-up, and those who stopped early will be interviewed within a month of doing so.

Topic guides will be developed for each set of interviews to ensure consistency across data collection. The therapist and study participant guides will be developed in parallel to ensure key areas are discussed with both practitioners and patients. This will help compare findings across the interviews, highlighting similarities and differences between the views and experiences of patients and practitioners, and increasing the confidence with which study conclusions can be drawn. With interviewee consent, the interviews will be audio recorded and transcribed verbatim.

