**Trial registration number:**

ISRCTN31976295.

Strengths and limitations of this studyThis is the first study to investigate the feasibility of conducting a large multicentre randomised controlled trial (RCT) of eye movement desensitisation and reprocessing (EMDR) for the prevention of psychosis in people with at-risk mental state.The study includes qualitative work to explore therapists and patients’ views of the treatment offered/received.Therapy sessions follow an EMDR protocol specifically designed for people with psychosis.The decision to change the study design to a single-arm trial may limit our ability to draw robust conclusions about recruiting to an RCT.

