### Objectives

The overarching aim of this study is to establish whether it would be feasible to conduct a large multicentre RCT to evaluate the clinical and cost-effectiveness of EMDR to prevent the onset of psychosis in people with an ARMS. The study has the following objectives:

To estimate the rate of recruitment and retention to inform the large-scale RCT.To refine the eligibility criteria, screening and recruitment procedures.To optimise the EMDR protocols and learn about the factors which affect the implementation of EMDR.To explore patients and therapists’ views of EMDR as a treatment for ARMS.To investigate patients and therapists’ views of the study design and study materials.To understand what TAU consists of for patients with ARMS.

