### Feasibility trial status

Recruitment to this study opened in May 2018, and closed in May 2020. At the time of writing (July 2020), 14 participants have been recruited to the study. We expect to finish follow-up data collection by May 2021.

This article describes protocol version 4, dated 2 August 2019. When all regulatory approvals had been received, the protocol was version 1, dated 11 January 2018. Since then, two major amendments have been made with changes to incorporate additional qualitative work, decrease the sample size and change the study design from an RCT to a single-arm trial. The latter change took place in July 2019 prior to which we had recruited six participants.

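### Since July 2019 consent is to assured EMDR, no listed interview topic or feasibility outcome addresses willingness to be randomised, and the plan may pool consent across the two offers

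*Protocol article*

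**What the plan says.** All places are in the Protocol article.

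- *Objectives*: the aim is to establish whether a large RCT is feasible. The first objective is "To estimate the rate of recruitment and retention to inform the large-scale RCT". The fifth is to learn what patients and therapists think of the study's design as well as its materials.
- *Study design*: "All participants will be offered EMDR, and will be assessed at baseline, 4, 8 and 12 months of follow-up as described below".
- *Challenges to recruitment*: the study began as an RCT of EMDR against TAU. "Therefore, from July 2019, all participants recruited to the study were offered EMDR".
- *Feasibility trial status*: "The latter change took place in July 2019 prior to which we had recruited six participants". "At the time of writing (July 2020), 14 participants have been recruited to the study". Recruitment had closed in May 2020.
- *Qualitative data collection*: participant interviews "will explore their views and experiences of the treatment received, identify how treatment delivery could be refined to increase its acceptability and how study materials" can be made better. Among those refusing, "up to 10 individuals who declined to take part in the trial will be interviewed to explore their views and understanding of the study and" the therapy, with their reasons for refusing. Topic guides are still to be developed.
- *Quantitative data analysis*: if those randomised and those entering the single-arm phase do not differ at baseline, their data are combined for the feasibility summaries. The first of these is the proportion consenting.
- Strengths and limitations list: "The decision to change the study design to a single-arm trial may limit our ability to draw robust conclusions about recruiting to an RCT".

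**The concern.** Agreeing to a therapy one is certain to be offered is a different decision from agreeing to have chance decide between that therapy and TAU. *Challenges to recruitment* describes TAU as heterogeneous, running from discharge back to the referrer or signposting through to CBT, family intervention or psychoeducation. Consent after July 2019 therefore does not measure consent to an RCT, and refusals after that date are refusals of a study without randomisation.

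Two features of the plan leave this gap open. First, Objective 5 covers the study design, but the participant topics as listed carry over only the study materials. A future RCT is named as a topic only for therapists, and only for the resources they would need. Second, the pooling rule would merge the consent proportions of the two phases into one figure. That figure would then go into RCT planning although it describes neither offer.

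**Working it through.** **1. The plan's own precision figures.** *Sample size and feasibility of recruitment* gives 45% to 88% for 70% completion and 50% to 91% for 75% retention, with n = 20. The exact (Clopper-Pearson) interval is 45.7% to 88.1% for 14/20 and 50.9% to 91.3% for 15/20. The stated figures are reproduced to within one point. They concern completion and retention; the article gives no precision for consent.

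**2. Recruits under each offer.** Six joined before the switch and 14 − 6 = 8 after it. So 6/14 = 43% consented to randomisation and 8/14 = 57% to assured EMDR.

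**3. What the first phase can say about consent to randomisation.** The number approached is not given. With assumed denominators and the plan's exact method:

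| Approached before July 2019 (assumed) | Consent | Exact 95% CI |
|---|---|---|
| 10 | 6/10 = 60% | 26% to 88% |
| 20 | 6/20 = 30% | 12% to 54% |
| 30 | 6/30 = 20% | 8% to 39% |

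There is some information, but very little.

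**4. What pooling does.** With n₁ and n₂ approached, the pooled proportion is (6 + 8)/(n₁ + n₂), an average of the two consent proportions weighted by numbers approached. With assumed denominators:

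- n₁ = 20, n₂ = 20: 30% and 40%; pooled 14/40 = 35%, which is 5 points above the randomised-phase figure.
- n₁ = 20, n₂ = 10: 30% and 80%; pooled 14/30 = 47%, which is 17 points above it.
- n₁ = 15, n₂ = 20: 40% and 40%; pooled 14/35 = 40%, no distortion.

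The size of the error depends on denominators that the article does not give. The pooling condition does not guard against it. Baseline characteristics are compared among people who entered the study, so similarity there says nothing about what share of those invited agreed. With 6 against 8 people, finding no difference is also weak evidence of similarity.

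**5. Whether the recruitment rates settle it.** May 2018 to July 2019 is about 14 months: 6/14 = 0.43 per month. July 2019 to May 2020 is about 10 months: 8/10 = 0.80 per month. The ratio is 0.80/0.43 = 1.9. For the interval, treat the counts as Poisson and condition on the total of 14. The exact limits for 8/14 are 0.289 and 0.823. Converting with p/(1 − p) × 14/10 gives 0.289/0.711 × 1.4 = 0.57 and 0.823/0.177 × 1.4 = 6.5. The data fit no effect of the offer or a large one. The rates also depend on how many patients were identified and on other changes, such as the widening of the recruitment window from 3 to 12 months, for which no date is given.

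**6. Scale of the step to an RCT.** If a share *a* of those accepting assured EMDR would also accept randomisation, RCT consent is *a* times the single-arm figure, a shortfall of 1 − *a*. For illustration only, *a* between 60% and 90% gives a shortfall of 40% to 10%. Nothing in the article supports any particular value.

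**The case against.** The strongest reply is that this argues from one sentence of a condensed article. The topic guides are not shown, Objective 5 expressly covers the study design, and *Qualitative data analysis* lets early interviews shape later ones. Questions about randomisation may therefore be asked. That stands as far as it goes: the article does not establish that the guides omit the subject. It does not answer the mismatch between Objective 5 and the topics as listed, and it does not touch the pooling rule, which is written out.

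A reader might infer that the study gathers nothing on willingness to be randomised. The article does not support this. Six people consented under randomisation, and all participants are to be interviewed. Anyone who declined before July 2019 was declining an RCT, and the expression-of-interest form and decliner interviews collect reasons.

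A reader might also infer that acceptance of randomisation is the main recruitment unknown. *Challenges to recruitment* says otherwise: the primary cause was that far fewer at-risk patients were identified than expected, and only three of six early intervention teams could support the study. The additional qualitative work is aimed at those problems. Nowhere is refusal of randomisation or of TAU reported as an obstacle.

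The authors also disclose the limitation of the single-arm change. Disclosure warns the reader, but it does not stop a mixed consent figure from being produced.

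**Conclusion.** The point holds in a limited form. After the switch, no listed participant topic or feasibility outcome specifically addresses willingness to be randomised or to accept TAU, although the aim and Objectives 1 and 5 call for it. The rule permitting a pooled consent proportion rests on a condition that cannot justify it.

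The size cannot be fixed from the article. Under the assumed denominators above, pooling moves the figure by 0 to 17 points from the randomised-phase value, and that value itself has an interval some 30 to 60 points wide. The rate ratio of 1.9 (0.6 to 6.5) should not be read as evidence that the prospect of TAU deterred people. The allocation ratio of the randomised phase is not stated, so no particular chance of receiving TAU can be assumed.

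Calling the single-arm figure an upper guide assumes that nearly everyone who would accept randomisation would also accept assured EMDR, and that other recruitment conditions are comparable.

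**What to change.** 1. In *Quantitative data analysis*, exempt the consent proportion from pooling. Report it separately for the randomised and single-arm phases, each with its denominator and exact interval, whatever the baseline comparison shows. Describe the single-arm figure as an upper guide to RCT consent.
2. Add willingness to be randomised between EMDR and TAU (with TAU described), and the reasons, to the participant and decliner topic guides for interviews still outstanding.
3. Put the same question on the consent and expression-of-interest forms for any further recruitment. It can no longer be asked at consent of these participants, because recruitment closed in May 2020.

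Time for the second step is short. Interviews with participants who complete fall within a month of the 4-month follow-up, so someone recruited in May 2020 would be interviewed by about October 2020.

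The cost is a reporting rule, a topic-guide line and one form item. The phase-specific intervals will be wider than a pooled one. Answers about randomisation will be hypothetical and may overstate real willingness; those given after therapy may also be coloured by having received it. They would inform RCT planning without settling the question.
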